## Abstract

**Background:**

People living with HIV (PLHIV) present impaired muscle metaboreflex, which may lead to exercise intolerance and increased cardiovascular risk. The muscle metaboreflex adaptations to exercise training in these patients are unknown. The present study aims to investigate the effects of a supervised multimodal exercise training on hemodynamic and autonomic responses to muscle metaboreflex activation in PLHIV.

**Methods and design:**

In this randomized clinical trial protocol, 42 PLHIV aged 30–50 years will be randomly assigned at a ratio of 1:1 into an intervention or a control group. The intervention group will perform exercise training (3x/week during 12 weeks) and the control group will remain physically inactive. A reference group composed of 21 HIV-uninfected individuals will be included. Primary outcomes will be blood pressure and heart rate variability indices assessed during resting, mental stress, and activation of muscle metaboreflex by a digital sphygmomanometer and a heart rate monitor; respectively. Mental stress will be induced by the Stroop Color-Word test and muscle metaboreflex will be activated through a post-exercise circulatory arrest (PECA) protocol, being the latter performed without and with the application of a capsaicin-based analgesic balm in the exercised limb. Secondary outcomes will be heart rate, peripheral vascular resistance, stroke volume, cardiac output, blood lactate, anthropometric markers and handgrip maximal voluntary contraction. The intervention and control groups of PLHIV will be evaluated at baseline and after the intervention, while the HIV-uninfected reference group only at baseline.

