**Fig 3 pone.0265516.g003:**
[figure not shown]
Experimental design.

After a general medical examination and anthropometric measurements, participants will remain 30 min at rest in a supine position before performing a mental stress task and handgrip strength test. The mental stress task will provide information about the integrity of pathways of stress-induced sympathetic responses mediated by the central command. Maximal voluntary contraction (MVC) assessed by the handgrip test will be used to determine the loads applied during the metaboreflex activation protocol, and to detect possible strength differences between groups at baseline and after intervention. Subsequently, the muscle metaboreflex will be activated using a post-exercise circulatory arrest (PECA) protocol, during which blood lactate will be assessed. Then, a capsaicin-based analgesic balm (0.1%, FarmaSite, Itaúna, Brazil) will be applied over the exercising arm to stimulate the metabolically sensitive muscle afferents via TRPv1 receptors [27], and after 30 min of topical application, PECA will be repeated.

Primary outcomes will be BP and heart rate variability (HRV) indices reflecting autonomic modulation. Secondary outcomes will be the heart rate (HR), peripheral vascular resistance (PVR), stroke volume (SV), cardiac output (CO), blood lactate concentration, anthropometric markers, and handgrip MVC.

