### Mental stress test

To investigate the integrity of muscle metaboreflex efferent pathways, a mental stress assessment will be performed using the Stroop Color-Word test [31], which has been widely used for stress-induced sympathetic effects mediated by the central command, regardless of the muscle metaboreflex activation [32]. The test will be administered for 5 min by a single researcher that will display slides changing every 2 s, showing color names written in different colors. The volunteers will identify the word colors irrespective of the written information. Changes from rest in autonomic and cardiovascular outcomes will be recorded as outcomes.

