### Primary outcomes

#### Blood pressure

Systolic and diastolic BP will be assessed in the non-dominant arm using a digital sphygmomanometer (Omron HEM—7113, Kyoto, Japan) positioned around the proximal third of the non-dominant arm. Data will be assessed at rest, and every minute during mental stress and muscle metaboreflex assessments.

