#### Heart rate variability indices

The HRV indices reflect cardiac autonomic modulation. Beat-to-beat HR will be continuously recorded using a heart rate monitor (Polar V800; Polar^TM^ Electro, Kempele, Finland) [33] at rest, during the mental stress task, and muscle metaboreflex activation protocol. The signals will be transferred to the Polar Precision Performance Software (Polar Electro, Kempele, Finland). After replacing the non-sinus beat by interpolated data derived from adjacent normal RR intervals, times series data will be exported to Kubios^TM^ HRV program for analysis (Version 3.4, University of Kuopio, Kuopio, Finland).

Time domain variables will be: mean normal RR intervals (RRi), standard deviation of normal NN intervals (SDNN), square root of the mean squared successive differences from adjacent RRi (rMSSD), and percentage number of pairs of adjacent RRi differing by more than 50 ms from previous RRi (pNN50). SDNN, rMSSD, and pNN50 are acknowledged to reflect the parasympathetic modulation within short periods [34]. Spectral analysis will be performed by the Fast Fourier transform method, with frequency bands corresponding to low-frequency (LF: 0.04–0.15 Hz), high-frequency (HF: 0.15–0.40 Hz), and total power (TP; meaning LF plus HF) [35]. The LF and HF reflect a predominance of combined sympathetic-parasympathetic and isolated parasympathetic modulation, respectively [35], while LF: HF ratio will be adopted as a marker of sympathovagal balance.

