### Sample size calculation and statistical analysis

Sample size was calculated using GPower 3.1.9.4 (Universität Kiel, Kiel, Germany) to detect longitudinal differences between groups in systolic BP response due to metaboreflex gain. Considering a between-group difference of 3.5 mmHg (standard deviation of 4.6 mmHg) [23], 80% power and 5% significance level, and increasing the sample size by 50% to account for losses to follow up, a total of 21 participants in each group was calculated as necessary.

Descriptive analysis will consist of mean and standard deviation for continuous variables and percentage for categorical variables. Data normality will be checked by the Shapiro Wilk test, and data will be presented as mean and standard deviation or percentage, whenever appropriate. A cross-sectional comparison between PLHIV-T, PLHIV-C and CONT will be performed at baseline by means of one-way ANOVA (continuous) or chi-squared test (categorical).

Longitudinal effects of exercise training on primary and secondary outcomes will be evaluated through linear mixed models (LMM) including treatment (PLHIV-T or PLHIV-C) and time as fixed effects, and group *vs*. time interaction. LMM, which correlates with repeated measures over the time, allows an intention-to-treat analysis as it includes all observations of each one of the participants, regardless of losses to follow-up or noncompliance to exercise protocol. Residual plots of all models will be examined and the likelihood-ratio test will be used to compare and select random intercept or random slope models. Data analysis will be performed using Stata 13.0 (StataCorp, College Station, TX, USA), and in all cases the statistical significance will be set at *P* ≤ 0.05.

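### Ten unranked primary indices across four conditions, each tested at 0.05, leave the false-positive risk for a primary result well above 5%, although only one response was sized

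*Protocol article*

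**What the plan says.** All references are to the protocol article.

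- **Primary outcomes.** The abstract says: "Primary outcomes will be blood pressure and heart rate variability indices assessed during resting, mental stress, and activation of muscle metaboreflex". The body, under Experimental design, repeats the two families without ranking them or naming conditions: "Primary outcomes will be BP and heart rate variability (HRV) indices reflecting autonomic modulation".
- **Conditions.** The abstract describes the circulatory-arrest (PECA) test as "being the latter performed without and with the application of a capsaicin-based analgesic balm in the exercised limb". With rest and mental stress, that makes four conditions.
- **Indices.** Under Blood pressure: "Systolic and diastolic BP will be assessed in the non-dominant arm using a digital sphygmomanometer". The section on HRV indices lists four time-domain measures (RRi, SDNN, rMSSD, pNN50), three spectral measures (LF, HF and their sum, TP) and the LF:HF ratio.
- **Analysis.** Primary and secondary outcomes all go through the same linear mixed model with a group-by-time interaction, "and in all cases the statistical significance will be set at" P ≤ 0.05. No ranking or adjustment is given.
- **Sizing.** The sample size was calculated "to detect longitudinal differences between groups in systolic BP response due to metaboreflex gain". No other primary outcome has a sample-size basis.
- **Role of mental stress.** "To investigate the integrity of muscle metaboreflex efferent pathways, a mental stress assessment will be performed". The section adds that this stimulus acts independently of metaboreflex activation.

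**The concern.** The stated aim is the effect of training on responses to muscle metaboreflex activation. As written, a significant interaction for pNN50 at rest or LF:HF under the Stroop task has the same primary standing as the systolic BP response to PECA. With one primary test the false-positive risk would be 5%. With many unranked tests at 0.05, nothing in the text limits the risk for the set as a whole, and the supportive index and condition can be chosen after the results are known.

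Two of the four conditions also fit the aim poorly. Mental stress drives the reflex's efferent limb without activating the metaboreflex, so it helps interpret a PECA finding but is not itself evidence of a metaboreflex adaptation. Resting values do not measure a response to activation at all.

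**Working it through.** **Plan's own figure.** The article states no overall error rate, so there is none to reproduce. Its only related figure is 21 per group. The stated inputs (difference 3.5 mmHg, SD 4.6 mmHg, 80% power, 5% level, taken as two-sided) give, for two independent means, n = 2 × [4.6 × (1.960 + 0.842) / 3.5]² ≈ 27.1, so 28 per arm before the 50% increase. This does not match 21, which is a separate matter. The inputs are used here only in step 5.

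**1. Count.** Indices: 2 (BP) + 4 (time domain) + 3 (spectral) + 1 (ratio) = 10. Conditions: rest, mental stress, PECA without balm, PECA with balm = 4. Group-by-time tests: up to 10 × 4 = 40.

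**2. Expected false positives if training has no effect.** 40 × 0.05 = 2, whatever the correlation.

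**3. Independent tests.** The chance of at least one false positive is 1 − 0.95^k.

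- k = 40: 1 − 0.95^40 = 0.871
- k = 20 (both PECA runs only): 1 − 0.95^20 = 0.642
- k = 10 (one condition): 1 − 0.95^10 = 0.401

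For jointly normal test statistics, independence gives the highest value (Šidák's inequality), so 87% is a ceiling.

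**4. Correlated tests.** The indices overlap: TP is LF plus HF, LF:HF uses the same two components, and the stress and PECA outcomes are changes from rest. The documents give no correlations, so a common correlation r is assumed. With shared normal component u, density φ and distribution function Φ, the chance is

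1 − ∫ φ(u) [Φ((1.96 − √r·u)/√(1−r)) − Φ((−1.96 − √r·u)/√(1−r))]^k du

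| r | 40 tests | 10 tests in one condition |
|---|---|---|
| 0 | 87.1% | 40.1% |
| 0.3 | 74.5% | 35.1% |
| 0.5 | 57.2% | 28.7% |
| 0.7 | 37.5% | 21.3% |
| 0.9 | 18.4% | 12.8% |

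A less uniform assumption (correlation 0.7 within BP and within HRV, 0.2 between them, 0.5 between conditions), simulated with 100,000 draws, gives 62% for 40 tests.

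**5. Why adjusting over the whole set is not practical.** Bonferroni over 40 gives 0.05/40 = 0.00125 per test. On the plan's difference and SD, n = 2 × [4.6 × (3.227 + 0.842) / 3.5]² ≈ 57.2, so 58 per arm before losses. With 21 per arm, power would be about 22%, against 69% at 0.05 (normal approximation). Bonferroni over ten indices in one condition (0.005 each) needs 46 per arm before losses.

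**The case against.** **An unseen analysis plan may deal with multiplicity.** Adjustment methods are often left there, and their absence from an article would be no finding. Here, however, the article itself fixes the whole set as primary and the 0.05 level for all cases. A plan that ranked or adjusted would depart from that text. This objection does not remove the point.

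**Forty is an upper count.** No section lists forty models, and the tests overlap. This stands, so 40 is given only as a maximum.

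**A chance-positive result is likely.** A reader might infer this from the 87%. The documents do not support it: that figure needs independence, which these indices cannot have, and under strong correlation the risk falls below one half. What does hold is that it stays well above 5%.

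**Mental stress tests pathways outside the metaboreflex, and an effect on it would count as trial success.** A reader might infer this too. The Mental stress test section says the opposite of the first part: the task checks the reflex's own efferent pathways by another route. For the second part, no section defines a success criterion, and the hypothesis in the Introduction concerns metaboreflex activation. What remains is that the abstract places mental stress among the primary conditions.

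**The sized endpoint is identifiable.** It is, in the sample-size paragraph. What it lacks is any priority in the outcome definitions.

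**The data analyst is blinded to allocation and balm use.** This makes it harder to favour an index knowingly during analysis. It does not change the error rate of many tests at 0.05, nor prevent selection once the results are unblinded.

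**Conclusion.** The point holds. Followed as written, the article gives up to 40 overlapping tests unranked primary status at 0.05 each, with a sample-size basis for only one response. The chance of at least one false-positive primary result is bounded by 87% and is about 75% to 18% for assumed common correlations of 0.3 to 0.9. Even one condition alone gives about 35% to 13% over that range, and 40% if independent. These figures assume that training has no effect on any index, approximately normal test statistics and two-sided tests. The correlations are assumptions, so no single value should be quoted as the trial's error rate. Inflation above 5% does not depend on which value in that range is chosen. Mental stress and resting values should not carry the primary claim, because neither measures the response to metaboreflex activation.

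**What to change.** **Primary outcome.** Name one: the between-arm difference in change from baseline to week 12 in the systolic BP response, defined as the change from PECA rest to the occlusion phase, in PECA without balm, tested at two-sided 0.05. Fix the averaging window in advance. The article gives minute-by-minute readings and a three-minute occlusion but no summary, and the choice belongs to the investigators. The false-positive risk for the primary claim is then 5%.

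**Everything else.** Make diastolic BP, the HRV indices, resting values and PECA with balm secondary, either adjusted (for example by Holm) or labelled exploratory. Label mental stress a specificity control that helps interpret the PECA result.

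**If HRV must stay primary.** Choose one HRV index and condition, and test it at 0.05 only if systolic BP is significant. This fixed order also holds the overall error at 5%.

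**Cost.** Changes to the outcome and analysis wording, made before outcome data are examined by arm, and a matching registry entry if it differs (the registry record was not available for this review). Data collection does not change. The downside is that HRV loses its primary status or takes second place, which gives the autonomic part of the aim less weight.

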**Discussion:**

The findings of the present study may help to elucidate the muscle metaboreflex adaptations to exercise training in PLHIV.

**Trial registration:**

This study will be performed at University of Rio de Janeiro State following registration at ClinicalTrials.gov as NCT04512456 on August 13, 2020.

## Introduction

The Acquired Immunodeficiency syndrome (AIDS) is a chronic, potentially life-threatening condition caused by the Human Immunodeficiency Virus (HIV). Globally, 680,000 people have died from AIDS-related illnesses in 2020 and 1.5 million new infections occurred in that year [1]. Access to combined antiretroviral therapy (cART) has prevented around 12.1 million AIDS-related deaths since 2010, so that 38 million people are currently living with HIV [2].

Despite the increase in life expectancy, the combination of prolonged HIV infection and cART treatment may damage several physiological systems, thereby increasing the risk of non-AIDS related diseases [3, 4]. A recent review [4] revealed that cardiometabolic diseases consistently appeared among the most reported comorbidities in people living with HIV (PLHIV), whose rates of myocardial infarction, heart failure, pulmonary hypertension, sudden cardiac death and stroke are higher in comparison with uninfected subjects [5]. Additionally, increased sympathetic activity, which is a marker of poor cardiovascular prognosis [6] is often found among PLHIV at rest [7, 8] and after physical exercise [9].

During exercise, hemodynamic function mediated by autonomic activity is mainly regulated by the exercise pressor reflex (EPR) [10], which responds to muscle afferent signals from type III (mechanoreflex) and IV (metaboreflex) nerve endings [11, 12]. Those afferent neurons are sensitive to mechanical stimuli and metabolite accumulation, respectively [13]. The EPR increases the sympathetic stimulation to both heart and blood vessels, in order to meet the augmented metabolic demand of working muscles [14]. If muscle mechano- or metaboreflex is blunted, the increase in blood pressure (BP) may not be enough to assure appropriate muscle blood flow and oxygen supply, leading to premature fatigue and exercise intolerance [15, 16]. Considering that abnormal skeletal muscle reflexes play a significant role in limiting the exercise tolerance, as well as in increasing the cardiovascular risk during or after exercise [14], investigations on strategies capable to counteract those impairments are clinically relevant.

Exercise training seems to improve sympathetic activity control and/or abnormal cardiovascular responses to muscle metaboreflex activation in several chronic conditions [17–20]. Although very little information is available on the potential mechanisms by which exercise training favors the muscle metaboreflex, they seem to include a wide spectrum of adaptations, as increased muscle perfusion with lower metabolite accumulation, greater antioxidant capacity, and changes in the expression of receptors evoking metaboreflex (i.e., the transient receptor potential vanilloid receptor 1 –TRPv1) [21]. Individuals with impaired metaboreflex have deficiencies in one or more of those mechanisms, and therefore might be more responsive to exercise training than healthy individuals [21]. This is the case of PLHIV, who often present lactic acidosis [22] and attenuated pressor response to metaboreceptor stimulation [23].

Despite this, we could not find research investigating muscle metaboreflex adaptations and its underlying mechanisms to exercise training in PLHIV. This would be nonetheless useful to determine the potential impact of exercise training on mechanisms controlling autonomic modulation during exercise, which have prognostic value [24]. Thus, the aim of the present study is to describe the experimental protocol of a randomized controlled trial designed to investigate the effects of a multimodal supervised exercise program (i.e., aerobic, resistance and flexibility exercises) on hemodynamic and autonomic responses to muscle metaboreflex activation in PLHIV. In addition, potential mechanisms of exercise training adaptations in the muscle metaboreflex will be analyzed by assessing blood lactate concentration and activating TRPv1. We will test the hypothesis that a multimodal exercise training would be able to increase the neurocardiovascular responses during metaboreflex activation by reducing blood lactate levels at rest and increasing TRPv1 sensitivity.

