### Muscle metaboreflex activity assessment

Muscle metaboreflex will be activated by a PECA protocol, which has been shown to trap muscle metabolites in the exercising limb and to maintain stimulation of group IV muscle afferents without the activity of the central command and mechanoreflex [12]. PECA will consist of 13 min, as follows: 5 min of rest, 2 min of isometric handgrip exercise with the dominant arm with a load corresponding to 40% of MVC, 3 min of vascular occlusion, followed by 3 min of recovery. Vascular occlusion will be applied in the exercised limb by inflating a cuff at 240 mmHg 5 s before the end of exercise, and then deflating it in the 3-min recovery. During PECA, the volunteers will be in a sitting position, and shall avoid performing the Valsalva maneuver and any movement, except for the handgrip. Changes from rest during PECA will be calculated for autonomic and cardiovascular outcomes.

Prior to PECA, a brief familiarization with the handgrip exercise will be allowed. Handgrip force exerted will be placed in front of the subjects to guide the contraction intensity. Vascular occlusion in PECA will be applied using a nylon cuff size 11 x 85 cm connected to a pneumatic cuff inflator Hokanson TD312 (D. E. Hokanson^TM^ Inc, Bellevue, Washington, USA) placed around the proximal third of the dominant arm. A vascular Doppler probe (DV 610B Medmega Industria de Equipamentos Medicos, Franca, SP, Brazil) will be placed over the brachial artery (dominant arm) to capture the auscultatory pulse and confirm the vascular occlusion during the PECA protocol. The Fig 4 details the PECA protocol.

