In the present protocol, the muscle metaboreflex will be activated by PECA, which is a non-invasive and non-pharmacological method widely used to isolate the metabolic component of ergoreflex, by arresting blood flow of the exercising muscles with a suprasystolic level cuff occlusion that traps the metabolic by-products of exercise within the muscles after the cessation of exercise [45–47]. Of note, PECA will be originally employed in combination to the topical application of a capsaicin-based analgesic balm over the exercising arm. The capsaicin is an active component of chili peppers targeting the TRPv1, which are important mediators of the metabolic stimulation of EPR [27]. Evidence has recently shown that a topical application of a capsaicin-based analgesic balm prior to the test attenuated the pressor and muscle sympathetic nervous activity responses to PECA [27]. However, capsaicin-based analgesic balms to assess exercise training-related adaptations on muscle metaboreflex have never been used. Another important aspect of this study is the multimodal characteristic of the exercise training protocol (e.g., aerobic and resistance exercises), as most studies using this modality of training have found benefits in EPR among other populations [17–19, 48], while those including only resistance training failed to observed similar adaptations [49, 50].

The present study protocol has some limitations. Firstly, autonomic modulation will be assessed by HRV. Although HRV has the advantage of being a simple, non-invasive method capable of assessing dynamic changes in the autonomic control of heart rate [51], more objective measurements of muscle sympathetic outflow, such as microneurography would provide more specific and direct information. Moreover, it will not be possible to control the diet and sleep habits of participants. Despite this, the present study might extend the current knowledge by demonstrating whether a supervised multimodal exercise training would be capable to improve the muscle metaboreflex among PLHIV. In addition, we also intend to provide new insights into the mechanisms potentially underlying the exercise-induced changes in the muscle metaboreflex, by assessing the influence of TRPv1 receptors, blood lactate concentration, and hemodynamic outcomes (e.g., HR, SV, CO, and PVR).

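### The stated model has no balm term and no balm contrast is defined, so the TRPv1 hypothesis is not tested by the analysis as written, and its supporting direction is not fixed

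*Protocol article*

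**What the plan says.** All references are to the protocol article.

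- **Hypothesis (Introduction).** Training is expected to raise neurocardiovascular responses during metaboreflex activation by "reducing blood lactate levels at rest and increasing TRPv1 sensitivity".
- **Measurement (Abstract, Methods and design).** PECA is "performed without and with the application of a capsaicin-based analgesic balm in the exercised limb". Under Experimental design, the balm test follows the test without balm at the same visit, 30 minutes after application.
- **Outcome definition (Muscle metaboreflex activity assessment).** "Changes from rest during PECA will be calculated for autonomic and cardiovascular outcomes". No section defines an outcome that sets the two PECA tests against each other.
- **Model (Sample size calculation and statistical analysis).** Primary and secondary outcomes are analysed with linear mixed models "including treatment (PLHIV-T or PLHIV-C) and time as fixed effects", with the group-by-time interaction. Balm condition is not mentioned there. In the analysis text it appears only under Masking and blinding, as something the analyst will not know.
- **What the balm does.** Experimental design says it is applied "to stimulate the metabolically sensitive muscle afferents via TRPv1 receptors". The Discussion says earlier evidence showed that it "attenuated the pressor and muscle sympathetic nervous activity responses to PECA". Both statements cite reference 27.

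**The concern.** TRPv1 sensitivity is not measured directly. It can be seen only through how much the balm changes the PECA response. A training effect on it is therefore a difference between arms, in the change over time, of the with-versus-without-balm difference. The stated group-by-time term does not contain that comparison.

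The direction is also open. A larger response with balm could be called higher sensitivity on the Experimental design wording, and a stronger attenuation could be called the same on the Discussion wording. If the sign is chosen after the data are seen, either result can be reported as support.

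At stake is one stated mechanistic hypothesis and the use of the balm, which the Discussion presents as new for studying training adaptations. The main question, whether training changes the metaboreflex response, is not at stake.

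**Working it through.** **1. What the stated model estimates.** Let θ₀ be the group-by-time effect on the PECA response without balm and θ₁ the same effect with balm. The TRPv1 hypothesis concerns θ₁ − θ₀.

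| Use of the stated model | What the interaction estimates |
|---|---|
| PECA without balm only | θ₀ |
| PECA with balm only | θ₁ |
| Both conditions pooled, balanced data | (θ₀ + θ₁)/2 |
| Same model fitted to D = with minus without balm | θ₁ − θ₀ |

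Only the last row answers the hypothesis, and D is not defined in the article. The lactate half of the hypothesis has no such gap: a sample at minute 5 of PECA, the end of the rest period, is a single outcome that fits the stated model directly.

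**2. Direction.** Write D as above.

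- If the balm adds stimulation to the afferents, more sensitive receptors suggest a larger (more positive) D.
- If the balm attenuates the pressor response, more sensitive receptors suggest a stronger attenuation, so a more negative D.

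No section says which reading applies.

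**3. Order.** The balm test is always second and no placebo balm is described. The within-visit D is then balm effect plus order effect. If the order effect is common to both arms and visits, it cancels to first order in the between-arm comparison of the change in D. It does not cancel in D itself.

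**4. Size, if two separate fits were compared by significance.** Inputs: 80% power and a 5% level from the sample size section, taken as two-sided because sidedness is not stated; equal true effects in both conditions; correlation r between the two test statistics, which is assumed. At 80% power the mean of each z statistic is 1.96 + 0.84 = 2.80.

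P(exactly one significant) = 2 × [P(|Z₁| ≤ 1.96) − P(|Z₁| ≤ 1.96 and |Z₂| ≤ 1.96)]

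At r = 0 this is 2 × 0.80 × 0.20 = 0.32. From the bivariate normal distribution:

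| r | 0 | 0.5 | 0.7 | 0.9 |
|---|---|---|---|---|
| Trials with discordant results | 32% | 23% | 17% | 10% |

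**5. Precision of the proper contrast (illustration).** Assumptions not in the document: 4.6 mmHg is the SD of the change in each condition, ρ is the correlation between conditions, and the true contrast is 3.5 mmHg, which is as large as the whole between-group difference the trial is sized for. Then SD of D = 4.6 × √(2(1 − ρ)).

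| ρ | SD of D (mmHg) | Power, 21 per arm | Power, 14 per arm |
|---|---|---|---|
| 0 | 6.51 | 40% | 28% |
| 0.25 | 5.63 | 50% | 35% |
| 0.5 | 4.60 | 67% | 49% |
| 0.75 | 3.25 | 93% | 78% |

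These are two-sided t-tests. Fourteen per arm is 21 with the stated 50% increase removed (21/1.5 = 14). At ρ = 0.5 the SD equals the 4.6 mmHg used for sizing, so D is then exactly as precise as a single-condition comparison; below 0.5 it is less precise. Whether 21 per arm delivers the stated 80% for the main comparison is a separate matter, and steps 1 to 3 do not depend on it.

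**The case against.** The strongest reply is that this is detail for a fuller analysis plan. The article is condensed, the contrast is mechanistic rather than primary, and blinding the analyst to balm use shows that the condition will be a variable in the data set. This has some force, and an unseen plan may well define the contrast. But the article does more than stay silent: it fixes the model's terms for all primary and secondary outcomes and fixes the PECA outcome as change from rest, and neither matches the hypothesis it says will be tested.

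Three stronger readings are tempting, and the document does not support them.

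- **That the hypothesis cannot be tested.** It can. The same model fitted to D, or extended by a three-way term, tests it with the planned data.
- **That the authors will compare two P values.** A reader might infer this from a model without a balm term, but no passage plans separate fits per condition or such a decision rule. The discordance figures show only what would follow if it were done. They count disagreement in both directions and rest on an assumed correlation.
- **That the article predicts opposite effects of the balm.** One statement gives the intended action on the afferents; the other reports an earlier study's effect on the reflex response. Neither is worded as this trial's expected result, and stimulating a receptor does not logically exclude a smaller later response. They are unreconciled, not strictly contradictory.

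The fixed order is likewise no flaw in the randomised comparison. It is a reason not to interpret the within-visit difference alone.

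**Conclusion.** The point holds in a limited form. The analysis as stated does not estimate a training effect on the balm-induced change in the PECA response, although the Introduction says that hypothesis will be tested. The direction that would count as increased TRPv1 sensitivity is not fixed. Both conclusions follow from the text alone and need no numerical assumption.

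The size is conditional. Informal comparison of two separate fits would give discordant significance in about 23% of trials with no TRPv1 change at all, given the stated 80% power, a two-sided 5% level and an assumed correlation of 0.5; the range is 10% to 32% for correlations from 0.9 to 0. The plan should be corrected before analysis, but the main training effect on PECA without balm is unaffected.

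**What to change.** 1. Define, for each participant and visit, D = PECA response with balm minus PECA response without balm, each response being the change from rest already planned.
2. Fit the stated treatment-by-time model to D. Equivalent choices are to compare week-12 D between arms adjusting for baseline D, or to add balm and its interactions, up to treatment-by-time-by-balm, to the model.
3. Reconcile the statements about the balm in Experimental design and the Discussion, and state before analysis which sign of D means higher TRPv1 sensitivity.
4. Base the TRPv1 claim only on this randomised between-arm contrast, not on the within-visit difference and not on significance in one condition but not in the other.

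The cost is analysis wording and one more planned contrast; no new measurement is needed. The downside is precision: the contrast may be less precise than the main comparison (when the two conditions correlate below 0.5, under the assumptions shown). It should be reported with its confidence interval, and a null result should not be read as evidence of no TRPv1 effect.
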